**Synopsis**

# TITLE: A phase I trial to assess the safety and feasibility of administering plasmid DNA carrying multiple HIV-1 genes together with dermal electroporation

**Objectives**

*Primary*

Is it safe and tolerable to immunize with seven or eleven DNA plasmids carrying HIV-1 genes with electroporation?

*Secondary*

1. Is it possible to increase immunogenicity of a DNA vaccine delivered intradermally and to reduce the number of injections needed by using electroporation?
2. Will electroporation improve/alter the quality of the immune responses induced by the HIV-1 DNA plasmids?
3. Is it possible to obtain similar immune reactivity by replacing two intramuscular boosts using MVA with two intradermal injections of HIV-1 DNA plasmids together with electroporation?
4. Can electroporation increase immunogenicity of all included DNA plasmids to permit mixing of all vaccine plasmids instead of delivering them as two different entities?
5. Will additional DNA plasmids broaden the anti-HIV-1 immune response?

**Study participants**

The study population consists of 48 healthy adults who are not infected by HIV. Subjects will be men or women, 18 to 40 years of age. Volunteers must not be engaging in high-risk behaviour for HIV (i.e., drug injection or sex with HIV positive partner). Participants will agree to practice safer sex to avoid infection with sexually transmitted infections and to use contraceptives to prevent pregnancy. For men this will mean consistent condom use and encouragement for partners to use oral contraception or IUD and for women mandatory oral contraception, IUD use or equivalent contraception in addition to consistent condom use.

Number of volunteers: 48 volunteers

Clinical site: South Stockholm General Hospital, Stockholm, SWEDEN

Clinical laboratories: Karolinska University Hospital, Huddinge, SWEDEN

Immunology and virology

laboratories: The Swedish Institute for Infectious Disease Control, Stockholm,

SWEDEN

*Study design*

| **Group** | **N** | **Mode of Immunization**  **(w 0, 6 , 12)** | **Mode of delivery** | **Left arm (Ampoules 1**  **env)** | | **Right arm (Ampoules 2**  **gag, Rtmut)** | **Boost immunization**  **(w 36 and 60)** |
| --- | --- | --- | --- | --- | --- | --- | --- |
| B1 | 10 | Id  ZetaJet® | No electroporation | 1 inj 100µl  0,3 mg DNA* | 1 inj100µl  0,3 mg DNA* | | 1 im inj needle  MVA 108 pfu |
|  | 2 | Id  ZetaJet® | No electroporation | 1 inj 100µl saline | 1 inj 100µl saline | | 1 im inj needle  100µl saline |
| B2 | 10 | Id  ZetaJet® | electroporation | 1 inj 100µl  0,3 mg DNA* | 1 inj 100µl  0,3 mg DNA* | | 1 im inj needle  MVA 108 pfu |
|  | 2 | Id  ZetaJet® | electroporation | 1 inj 100µl saline | 1 inj 100µl saline | | 1 im inj needle  100µl saline |
| B3 | 10 | Id  ZetaJet® | electroporation | 1 inj 100µl  0,3 mg DNA* | 1 inj 100µl  0,3 mg DNA* | | 2 id inj Zetajet®,  tot. 0,6 mg DNA + electroporation |
|  | 2 | Id  ZetaJet® | electroporation | 1 inj100µl saline | 1 inj100µl saline | | 2 id inj Zetajet®,  tot 200µl saline +  electroporation |
| B4 | 10 | Id  ZetaJet® | electroporation | 1 inj100µl  0,3 mg DNA** mixed ampoules | 1 inj100µl  0,3 mg DNA** mixed ampoules | | 1 im inj needle  MVA 108 pfu |
|  | 2 | Id  ZetaJet® | electroporation | 1 inj100µl saline | 1 inj100µl saline | | 1 im inj needle  100µl saline |

*) 7 DNA plasmids **) 11 DNA plasmids.

Immunizations will be given as prime injections (HIV DNA) at weeks 0, 6 and 12 and as boost injections (MVA) at week 36 and week 60.

MVA: The HIV MVA-CDMR is produced by the US Military HIV Research Program, Rockville, Maryland, USA. This vaccine contains the live attenuated Modified vaccinia virus Ankara with recombinant HIV-1 genes.

ZetaJet® is a jet stream delivery device produced by Bioject Medical Devices that is used to administer DNA plasmids in skin or muscle. The ZetaJet® is used for the id administration of the HIVIS DNA just before electroporation. Contact; [name], Bioject Medical Technologies, Inc., [name], [name]. Toll Free: [contact]

*Description of electroporation*

We are proposing to use a device, DermaVax™ (Cyto Pulse Sciences, Inc.) adapted for dermal electroporation in conjunction with intradermal injections of plasmid DNA. This technique uses microelectrodes to prevent skin damage and reduce the discomfort that is associated with intramuscular electroporation. The use of intradermal injection + electroporation, in contrast to intramuscular treatment, also allows for direct ocular inspection of the treatment sites.

DermaVax™is produced by Cyto Pulse Sciences, Inc, [name], [name] 21061, USA; a company developing novel electric field based technologies for cancer treatment, gene therapy and infectious disease applications. The devise aids in introducing plasmids intracellularly for increased expression.

*Endpoints*

Primary endpoints:

1. The safety of immunization with the seven or eleven DNA plasmids carrying HIV-1 genes and concomitant electroporation will be assessed by clinical signs and standard biochemical and haematological laboratory tests. Any grade of severity will be considered for causality by the vaccine. A fourfold increase in two consecutive tests will be considered significant.
2. The alternative boost immunization (im with MVA or id with HIV DNA + electroporation) will be evaluated by assessing local (pain and cutaneous indurations), general (fever, chills, headache, nausea, vomiting, malaise, myalgia) and other unsolicited adverse events within 28 days. Any grade III or IV event will be taken as an indication that the treatment in the specific arm is less tolerable.

Secondary endpoints:

A qualitative evaluation of cellular and humoral immune responses against antigens representing the different immunogens will be performed.

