**1.5 Endpoints**

*1.5.1 Primary:*

1. The safety of immunization will be assessed by clinical signs and standard biochemical and haematological laboratory tests where any worsening of the severity grade will be considered for causality with the vaccine.
2. The immunization will be evaluated by assessing local (pain, cutaneous reactions including indurations), general (fever, chills, headache, nausea, vomiting, malaise, myalgia) and other unsolicited adverse events within 28 days. Any grade III or IV event will be taken as an indication that the group of patients tolerate this schedule less well.

The primary safety parameters will be graded:

- Local adverse event Grade 3 or above (pain, cutaneous reactions including indurations).
- Systemic adverse event Grade 3 or above (temperature, chills, headache, nausea, vomiting, malaise, or myalgia).
- Other clinical or laboratory adverse events Grade 3 or above confirmed at examination or on repeat testing.

Any event attributable to vaccine leading to discontinuation of the immunisation regimen must be documented. Data on local and systemic events listed above will be solicited with specific questions or using a diary card for 7 days following each immunisation. Data on other clinical events and laboratory events will be collected with an open question at each visit and through routinely scheduled investigations.

*1.5.2 Secondary:*

A qualitative evaluation of cellular responses against peptides representing the different immunogens will be performed primarily by the ELISPOT technique. Additional testing will be performed by intracellular cytokine staining quantifying IFN-, IL-2, TNF- and MIP-1 production by CD4 and CD8 T cells, lymphoproliferation against inactivated HIV using fresh cells and multi-colour intracellular cytokine staining using cryopreserved cells for assessment of multiple T cell effector functions including immunophenotyping of responding cells. Testing for binding antibodies and, if binding antibodies are present, also neutralizing antibodies will be performed.

Group B1 will be compared with the id only group in the HIVIS study (Group A in HIVIS trial) for evaluation of the lower dose of HIV DNA (0.6 vs 1.0 mg).

Group B2 will be compared with Group B1 for evaluation of the lower dose of HIV DNA with and without electroporation.

Group B3 will be compared to the group B2 for the evaluation of HIV DNA as a boost compared to boosting with HIV MVA.

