### 8 Statistical considerations

**8.1 Sample size**

Safety: By the end of this study an additional (compared to previous clinical trials) 40 participants will have been exposed to HIV DNA and 30 the HIV MVA. In addition 36 individuals will have been exposed to 3 electroporation procedures and will be described in the qualitative safety evaluation. This is considered sufficient for the planning of continued studies.

Immunology, secondary endpoints: The size of the groups (10+2) and the comparisons described below, 8.2, is judged to be sufficient in a descriptive study in order to formulate the hypothesis to be tested in a planned trial in Tanzania.

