**8.2 Analysis**

All safety end-points will be graded by the Clinical Investigator and reviewed by the Trial Management Group. Any queries about grade and relationship to study product that cannot be resolved will be referred to the Trial Coordinating Committee for a final decision.

The primary end-points:

1. The safety of immunization with the seven or eleven DNA plasmids carrying HIV-1 genes will be assessed by clinical signs and standard biochemical and haematological laboratory tests where any worsening of the severity grade will be considered for causality with the vaccine.
2. The immunization will be evaluated by assessing local (pain, cutaneous reactions including induration), general (fever, chills, headache, nausea, vomiting, malaise, myalgia) and other unsolicited adverse events within 7 and 28 days. Any grade 3 or 4 event will be taken as an indication that the arm is less tolerable.

The secondary endpoints

The secondary endpoint (immunogenicity) will primarily be assessed by IFN-γ ELISpot 2 weeks after the third DNA immunization, the fourth DNA or first MVA immunization and after the fifth DNA or second MVA immunization. Both number of responders and magnitude of responses will be tested for significance. Additional studies will be performed at other time points using other assays such as intracellular cytokine staining, lymphoproliferation assays, epitope mapping, binding (and if indicated) neutralization antibody assays.

Group B1 will be compared with the id only group in the HIVIS study (Group A in HIVIS trial) for evaluation of the lower dose of HIV DNA (0.6 vs 1.0 mg).

Group B2 will be compared with Group B1 for evaluation of the lower dose of HIV DNA with and without electroporation.

Group B3 will be compared to the group B2 for the evaluation of HIV DNA as a boost compared to boosting with HIV MVA.

Group B4 is will be compared to groups B1-B3 to show if priming with additional HIV-related plasmids will increase immunogenicity to any of the included antigens.

Figures/tables will be prepared including all participants’ results.

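### The primary safety endpoint differs between the synopsis and sections 1.5.1 and 8.2, and its single-event rule ranks arms without a comparator

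*Protocol*

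**What the plan says.** The primary endpoint is written out three times.

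- **Synopsis, Endpoints.** For laboratory and clinical safety: "Any grade of severity will be considered for causality by the vaccine", followed by "A fourfold increase in two consecutive tests will be considered significant". For tolerability: "The alternative boost immunization (im with MVA or id with HIV DNA + electroporation) will be evaluated by assessing local" and general reactions and unsolicited events within 28 days.
- **Section 1.5.1.** For safety, "any worsening of the severity grade will be considered for causality with the vaccine", with no fourfold rule. The tolerability item refers to the immunisation without limiting it to the boost. This section alone lists graded safety parameters (grade 3 or above, with other clinical and laboratory events confirmed at examination or on repeat testing).
- **Section 8.2.** The same grade-worsening wording as 1.5.1, no fourfold rule, and again no limitation to the boost.

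All three carry nearly the same decision rule. Section 8.2 puts it as "Any grade 3 or 4 event will be taken as an indication that the arm is less tolerable".

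Section 8.1 justifies the size by exposure: "40 participants will have been exposed to HIV DNA and 30 the HIV MVA", and "36 individuals will have been exposed to 3 electroporation procedures". It calls the safety evaluation qualitative and gives no event rate, margin or error level.

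**The concern.** The primary objective asks whether seven or eleven plasmids given with electroporation are safe and tolerable. If the synopsis is followed, the tolerability endpoint looks only at weeks 36 and 60. At those visits B1, B2 and B4 receive intramuscular MVA by needle, and only B3 receives DNA with electroporation. Most of what the objective asks about would then fall outside its own tolerability endpoint. An analysis plan written from this protocol would have to choose between the versions.

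The two decision rules raise a separate question. The fourfold rule looks only upwards and does not say fourfold over what. The single-event rule delivers a comparative statement about an arm but compares it with nothing, so in groups of ten vaccine recipients a single unrelated event can decide the statement made about that arm.

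**Working it through.** **1. The three statements side by side**

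| Element | Synopsis | 1.5.1 | 8.2 |
|---|---|---|---|
| Laboratory trigger | any grade | any worsening of grade | any worsening of grade |
| Fourfold rule | yes | no | no |
| Tolerability scope | boost only | immunisation, not limited | immunisation, not limited |
| Any grade 3/4 event marks the arm | yes | yes | yes |

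**2. What the boost-only scope leaves out** (design table, section 1.2; products, section 1.4.1)

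- Eleven plasmids with electroporation: B4, weeks 0, 6 and 12 only. Assessed by the synopsis tolerability endpoint: never.
- Seven plasmids with electroporation: B2 prime (not assessed), B3 prime (not assessed), B3 boost (assessed).
- So 10 vaccine recipients (B3) of the 30 given DNA with electroporation would have any electroporated dose assessed for tolerability.

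**3. The fourfold rule**

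A fall is not an increase of any size, so falls in haemoglobin, platelets, neutrophils, lymphocytes or CD4 cannot meet it. For rises, take baseline as the reference (an assumption, since none is named) and use illustrative baselines within the section 1.3.1 entry limits:

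- Creatinine from 0.9 to 3.5 × the upper limit: 3.5 / 0.9 = 3.9, not significant.
- ALT from 0.3 to 1.2 × the upper limit: 1.2 / 0.3 = 4, significant if repeated, yet still inside the entry limit of < 1.25.
- ALT from just under 1.25 × the upper limit must reach about 4 × 1.25 = 5 before it counts.

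The grading scale is in an appendix not available here, so these values cannot be mapped to grades.

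**4. The single-event rule**

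Without assuming any rate:

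- One event in each arm marks all four arms as less tolerable at once.
- 1/10 against 0/10 gives opposite verdicts. Given one event among 20, it falls in either arm with probability 0.5, so the two-sided Fisher p = 0.5 + 0.5 = 1.00. At 4/10 against 0/10, p = 0.087. The first contrast below 0.05 is 5/10 against 0/10, p = 0.033.

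With an assumed background rate p per participant, the same in every arm, the chance that an arm of n is flagged is a = 1 − (1 − p)^n. The chance that exactly one of two such arms is flagged is 2a(1 − a).

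| p | n = 10 flagged | n = 12 flagged | exactly one of two arms of 10 |
|---|---|---|---|
| 0.5% | 4.9% | 5.8% | 9.3% |
| 1% | 9.6% | 11.4% | 17.3% |
| 2% | 18.3% | 21.5% | 29.9% |
| 5% | 40.1% | 46.0% | 48.1% |
| 10% | 65.1% | 71.8% | 45.4% |

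The n = 12 column applies only if events in the two saline recipients count against the arm, which the text does not settle. In the other direction, an arm of 10 with a true rate of 10% shows no event with probability 0.9^10 = 34.9%.

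**5. Exposure figures in 8.1**

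DNA: 4 × 10 = 40. MVA (B1, B2, B4): 3 × 10 = 30. Electroporation (B2, B3, B4): 3 × 12 = 36. All three stated counts reproduce. DNA together with electroporation: 3 × 10 = 30, of whom 20 receive seven plasmids and 10 receive eleven. With zero events, the two-sided 95% upper limit is 1 − 0.025^(1/n): 8.8% for 40, 11.6% for 30, 16.8% for 20 and 30.8% for 10.

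**The case against.** The trial is a descriptive phase I study. The rule speaks of an indication, not a test, and section 8.2 promises figures or tables with every participant's results. Relatedness is classified in section 5.2, can be referred for a final decision under 7.6.1 and 8.2, and is part of the halting criteria in 3.7.2. This limits the harm the single-event rule can do. It does not supply the comparator or relatedness condition that the endpoint sentence lacks.

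Several stronger readings are tempting, and the protocol does not support them:

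- **The plan is blind to cytopenia.** It is not. The fourfold sentence stands beside a grade-based review, and 1.5.1 and 8.2 use grade worsening. Falls in counts are considered for causality; the fourfold rule merely cannot call them significant.
- **The rules give wrong verdicts.** They can mislead. How often depends on a background rate the protocol does not give, and at 0.5% a harmless arm of 10 is flagged only about 5% of the time.
- **The observation windows conflict.** The synopsis and 1.5.1 say 28 days and 8.2 says 7 and 28. Since 1.5.1 itself collects solicited events for 7 days, 8.2 can reasonably be read as naming both.
- **The 40, 30 and 36 are wrong.** They reproduce. Section 8.1 does not claim that 36 received DNA with electroporation. All 36 are scheduled for three priming procedures, and the two further ones in B3 are visible in the design table.
- **B1 can serve as control for every arm.** B4 is recruited separately with its own randomisation list, so B1 is co-randomised only with B2 and B3.

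Some of the presentation could be left to an analysis plan. The contradiction in the endpoint itself could not, because that plan would inherit it.

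**Conclusion.** The inconsistency is established from the text alone. The synopsis differs from 1.5.1 and 8.2 on the scope of tolerability and on the fourfold rule. Its scope would leave eleven plasmids with electroporation without a tolerability assessment. Safety signs and laboratory tests for that group remain covered by the first primary endpoint, and diary data are collected after every immunisation. The gap is therefore in what counts as the primary endpoint, not in what is recorded.

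The fourfold rule is one-directional and has no reference value. The single-event rule can mislead: it can flag every arm at once, and it separates 1/10 from 0/10, which is no evidence of a difference. The flag rates for a harmless arm of 10 (about 5% to 65%, and 40% at a 5% rate) rest on an assumed background rate of 0.5% to 10% per participant, equal across arms and independent between participants.

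**What to change.** 1. Use one wording in the synopsis, 1.5.1 and 8.2, covering all immunisations and worsening of severity grade from baseline.
2. Delete the fourfold rule, or give it a reference value and reconcile it with the grading scale.
3. Replace the single-event verdict with the number and proportion of vaccine recipients per arm who have a grade 3 or higher event, for all events and for those at least possibly related, with exact 95% confidence intervals. Show these descriptively beside the saline recipients, noting that the eight saline recipients (4 × 2) differ in electroporation and boost procedure. Show B1 beside B2 and B3 only.
4. Optionally, add to 8.1 that 30 participants receive DNA with electroporation (20 with seven plasmids, 10 with eleven), with the zero-event upper limits of 11.6%, 16.8% and 30.8%. The existing counts can stay.

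The cost is protocol wording and a slightly less favourable statement of precision. No participants, visits or samples are added. It is best settled before the analysis plan goes to the DSMC under 7.7.4.

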**Introduction**

*General aims of the trial*

The HIV infection is one of the most lethal infectious diseases today. Around 30-40 million persons are infected, and may thus transmit the virus. A vaccine would be the most efficient way to stop transmission and in the long run eradicate disease (similar to what was achieved against smallpox). To vaccinate against HIV is difficult since a few particles may be enough to infect the host. The virus genome then remains incorporated in the infected cell and can replicate at any time after infection. The virus genome is variable and therefore immune responses to one subtype may not protect against virus of another subtype. Antibody responses are needed to neutralize the primary infectious virus and a cell mediated immunity is needed to eliminate the first infected host cells and, in the case of an infection, suppress the viral replication.

A vaccine based on the delivery of genetic material, either in the form of a plasmid or a viral vector, gives rise to a production of the vaccine antigen (protein) in the body of the vaccinee. A protein produced in this manner will be naturally processed (i.e. correctly folded and glycosylated) thus mimicking the proteins carried by the virus. To deliver the plasmid DNA by electroporation will permit a higher number of vaccine-plasmids to enter skin cells, which then start producing the vaccine antigen. These antigens are considered foreign to the host, and evoke both cellular and antibody immune responses. Therefore the proposed HIV vaccination protocol with electroporation should permit a lower dose of the HIV genes to be delivered and still induce a potent immune response. The mixture of genes from several subtypes of HIV will at the same time permit a broader immune response to several subtypes of HIV.

*Preliminary results*

A phase I trial (HIVIS 01/02) with a multi-subtype HIV-1 DNA vaccine boosted with a vaccinia vector (MVA) with the corresponding HIV-genes inserted into it, has been successfully conducted in our clinic in Sweden. The combination of DNA and MVA was proven safe and highly immunogenic as 34/37 (92%) of participants reached the primary endpoint of positive IFN gamma ELISPOT of whom 31 reacted to gag peptides and 24 to env peptide pools. Including also other assays of HIV-specific immune responses, 97% (all but one subject) of the cohort participants, developed HIV-specific immune responses. All DNA injections were given by the Biojector2000 needle-free device. Preliminary analysis indicates that ¼ the dose DNA given id primes an immune response equally as well as a ‘standard’ 4 mg dose given im, and that boosting with MVA could be achieved in the presence of vaccinia immunity. Volunteers above 40 years of age mounted a significantly lower immune response to the immunogens. It was also evident that the higher dose of MVA (108 pfu) delivered im gave better boosting of the DNA primed responses than when 107 pfu of MVA was given id. However, in order to administer the DNA intradermally, five shots with the Biojector were required at each immunisation time point. In contrast to the prominent T cell responses detected after immunization only weak anti-HIV antibody responses were observed (Sandström et al., 2008).

A further placebo-controlled phase II trial (HIVIS 03) in Dar es Salaam (MUHAS) of 60 non-infected individuals has confirmed the safety and immunogenicity of the HIVIS DNA and HIV MVA boost schedule. The study is now unblinded and analysis presented at the AIDS vaccine meeting in Paris 2009 (Bakari, et al., 2009). Since 1986 laboratory and clinical capacity building has taken place in Dar es Salaam, Tanzania, through the SIDA/Sarec TANSWED programme. This has led to the introduction of HIV vaccine studies in line with the Tanzanian National HIV Vaccine Strategic framework under the European Community program HIVIS, supported by both SIDA/Sarec and EU. An extension of this trial, TaMoVac has been funded by EDCTP. It is also anticipated that a further trial will be needed to introduce the technique for administration of vaccines (electroporation). This has passed through all the application steps for funding from EDCTP.

*HIV vaccine strategies under investigation*

There is a broad scientific consensus that a successful vaccine to prevent HIV-1 transmission must be able to elicit HIV-specific CD8+ cytotoxic T-lymphocytes (CTL) and also antibodies capable of neutralising primary HIV isolates (Nab). Present vaccine candidates against HIV-1 include: protein or peptide subunit vaccines with adjuvants; live-vector based vaccines; and plasmid DNA vaccines.

Subunit vaccines, such as highly purified recombinant monomeric HIV-1 envelope proteins elicit low or no virus-specific CTL, strongly binding but not broadly neutralizing antibody responses, even when adjuvanted with potent immunostimulants. Two HIV vaccine efficacy trials with HIV-1 subtypes B and E glycoproteins gp120 have been completed. The vaccine did not induce protection against HIV-1 infection, nor did it lower the viral load after infection. A phase III trial with the gp120 subunit vaccine combined with a canarypox vector encoding the same protein was shown to have a moderate protective effect of 31.2% (Rerks-Ngarm et al., 2009).

A phase IIB trial, termed STEP, of an adenovirus vector based vaccine carrying HIV-1 genes gag, pol and nef of subtype B was in 2007 terminated as the vaccine was shown to be ineffective and even associated with an increased transmission in uncircumcised MSM volunteers with pre-existing adenovirus immunity. At present, combining DNA vaccines and live-vector based vaccines in prime-boost regimens appears to be the most promising vaccine strategy. However, many issues remain to be addressed. One issue is the efficacy of the DNA immunization, which is the topic of this investigation. Another issue is that animal studies so far indicate that this approach might offer a limited protection from infection and also has the potential to lower the viral load post infection and potentially protect from development of disease. A reduction of the viral load of infected individuals could reduce the risk of HIV transmission. The focus on a lowering of the viral load (in contrast to the induction of sterilizing immunity) constitutes a change in paradigm in HIV vaccine development and has profound implications on vaccine efficacy trials.

HIV exists in many subtypes with different prevalence in different parts of the world. It was shown by several groups that infection or immunization with one subtype may induce immunity to a different subtype (Leandersson et al., 2000 and several papers thereafter). The level of conservation of the amino acid sequence between subtypes varies depending on what viral protein is analyzed and it is possible that it is warranted to include sequences from several subtypes for some of the viral proteins (e.g. envelope proteins). For some proteins it might be sufficient to include only one sequence (e.g. the polymerase gene). Today it is prudent to include antigens from the subtypes that are prevalent in the area where the vaccine in planned to be used. In the current trial in Tanzania env of subtypes A and C are included since these are the major subtypes present. Env of subtype B is included since it is closely related to subtype D that also is circulating in Tanzania. Subtype B is the dominating subtype in Europe and the US. Gag of subtypes A and B are included for the same reason. The vaccine is complemented with RT and rev to further broaden the anti-HIV-1 immune responses. The expanded 11 plasmid vaccine also contains nef, tat and protease of subtype B and gag of subtype C. Rev of subtype B is also included to augment the expression of the envelope genes. Env is desirable also in order to raise antibodies. Since it is highly variable it is prudent to try to match it as to the predominating subtypes. Gag and RT are known to give rise to potent CTL responses and are less likely to vary. A larger number of antigens will also increase the likelihood that an individual regardless of HLA type will react to more epitopes. Reactivity to an increased number of (gag) epitopes has been associated with lower viral load in infected vaccine recipients in the STEP study and strong gag-responses has also been shown in HIV-1 patients that are able to control viral replication (Kiepiela et al., 2007).

*Plasmid DNA-vectored genes* have been shown to induce primarily cell-mediated memory immune responses, but requires high doses to immunize humans when delivered im by conventional needle. Immune responses have been successfully boosted by immunogens included in various viral vectors, such as vaccinia, fowlpox or adenoviruses. However the doses of DNA that needs to be given are substantial and it would be a great advantage if a more efficient delivery mode/route can be found. We have recently shown, in HIVIS 01/02, that the proposed HIV DNA vaccine to be used in this study can prime as efficiently when used at a ¼ of the dose when administered intradermally with the Biojector 2000®, compared to intramuscular administration. Despite similar capacity to prime for a subsequent boost of MVA, the i.d. DNA prime alone induced responses in only 3/10 volunteers as compared to 7/9 after the im higher dose administration. Furthermore the id administration required 5 injections per immunization, which is impractical on a larger scale.

*Electroporation*is the use of a transmembrane electric field pulse to induce microscopic pores in the cell membrane. The pores allow macromolecules, such as DNA, to pass into the cell. The electropores are located primarily on the surfaces of cells which are closest to the electrodes. If the electric field pulse has the proper parameters, then the "electroporated" cells recover rapidly (the electropores reseal spontaneously), and the cells stay viable and can produce the vaccine protein. The time for the pathways to form is about one microsecond and the pores reseal within minutes thereafter. The Derma Vax™ Intradermal Delivery System (Roos et al., 2006 and 2009) primarily targets the dermis layer of skin. It utilizes a two-step process where the DNA plasmid is intradermally injected by needle or Biojector. Then an array of 2 rows of 6 needle electrodes of 2 mm in length is pressed against the skin, straddling the injection site and followed by the delivery of less than a second of electric pulses. The two main layers of the skin, the epidermis and dermis, contain numerous resident antigen presenting cells such as Langerhans cells and dermal dendritic cells, making the skin an attractive target for DNA immunization. After intradermal plasmid injection into skin, transfected cells are typically restricted to the epidermis. However, when electroporation is applied after the injection, larger numbers of epithelial, fibroblast and dendritic-like cells are transfected. Because of surface access, and because skin electroporation is relatively painless, this methodology is more suitable for human use than intramuscular electroporation. Several studies have shown pronounced augmentation of cell mediated and humoral responses to various antigens in small animals and non-human primates, with intramuscular or intradermal electroporation (Luckay et al., 2007; Hirao et al., 2007 and 2008; Cristillo et al.,2008; Bråve and Wahren., 2008). Clinical studies with HIV DNA plasmids have been initiated in the US using an intramuscular electroporation device (Vasan, 2009). However, muscular contractions can be very painful and this is avoided by the proposed intradermal mode of electroporation.

At present (January 2010) several clinical studies are ongoing with the use of electroporation: In the US with HIV plasmids, in Sweden with HCV plasmids and with Prostate specific antigen.

In the phase I HIVIS 01 study it was found to be safe to use the seven plasmids. This has also been the experience in the ongoing follow-up phase I/II study, HIVIS 03, in Tanzania. We now aim to improve on the DNA immunogenicity with electroporation to allow us to deliver fewer injections and augment the antibody responses. With this safety record, we are planning to proceed to an EDCTP funded phase II trial, TaMoVac, in Tanzania to study the promising modes of DNA delivery followed by MVA and/or boosted by heterogeneous HIV DNA. The rationale for the use of several subtypes in this trial is as delineated above.

